**Fig. 2 Fig2:**
[figure not shown]
Flow chart of the NUTRI-HAB trial

Randomisation will be stratified by need for rehabilitation services measured by the REHPA scale adapted from the National Comprehensive Cancer Network® Distress Thermometer [72]. On the REHPA Scale, participants indicate how close or how far they are from living the life they want after or in spite of their disease. A higher score indicates greater rehabilitation needs. The REHPA Scale was included in the nationwide survey. A certain score on the REHPA scale is not an inclusion criteria for the present trial, but randomisation will be stratified to ensure similar proportions of individuals with a score of ≥3 across the invitation lists. Participants will be randomised in STATA/IC 15.1 by a blinded researcher ([name]) who is not involved in the trial intervention or assessment of outcomes.

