### Participants

Participants will be recruited among respondents of a nationwide survey on late effects and health-related QOL in Danish patients treated for HNC 1–5 years following radiation therapy. The survey population was identified through The Danish Head and Neck Cancer Group’s (DAHANCA) national clinical quality database [37].

The survey was distributed in March 2019. Patients treated for HNC will be eligible for participation in the trial if they meet the following inclusion criteria:

Register-based information:
Have been diagnosed with cancer of the larynx, pharynx, or oral cavityHave completed curatively intended treatment with radiation therapy 1–5 years before survey distribution (1st of March 2014 to 28th of February 2018)Are aged ≥18 years

Self-reported information collected through the survey:
Have no active HNC or any other active cancer at the time for completion of the surveyAre self-reliant. Survey respondents are defined as self-reliant if they answered “Not at all” on the question “Do you need help with eating, dressing, washing yourself or using the toilet?” in The European Organization for Research and Treatment of Cancer’s (EORTC) QLQ-C30 questionnaire [38] on health-related QOLAre able to speak and understand DanishHave confirmed that they are interested in participating in a multidisciplinary residential nutritional rehabilitation programme at specific dates and given their permission to be contacted with further information. This inclusion criterion has been established to obtain permission and contact details for telephone contact and to narrow down the population for inclusion since the nationwide survey was distributed to almost 2000 individuals. By giving survey respondents the possibility to opt out for further contact regarding the trial, we reduce the number of inquiries to each respondent.

Potential recurrence of cancer during the trial will not lead to exclusion of participants. In the event of cancer recurrence in one or more participants, sensitivity analyses will be made to investigate whether this affects the trial results.

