### Inclusion and randomisation

Figure 2 shows the flow of the inclusion and randomisation process. Individuals who have responded to the nationwide survey within nine weeks from survey distribution and who meet the inclusion criteria will be randomised into invitation lists for intervention group or wait-list control group. The allocation ratio will be 1:1, and allocated individuals will be placed in random order on the numbered invitation list. Four residential rehabilitation programmes are scheduled, and each has a maximum capacity of 20 participants. Hence, a maximum of 40 participants in each group can be included. The first 40 individuals on each invitation list will receive further information about the trial and be invited to participate. Invitations will be sent electronically to e-Boks, a secure digital mailbox linked to the individual’s civil registration number. In Denmark, it is mandatory to have e-Boks unless a citizen applies for exemption. Individuals without e-Boks will receive the invitation through postal mail. If the invitation is declined, the next person on the given invitation list will be invited. If invited individuals do not respond, they will be contacted by telephone.

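### Stratifying by REHPA score ≥3 secures balance across the full invitation lists, but does not ensure it among the 36 to 40 people enrolled per arm

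*Protocol article*

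**What the plan says.** The procedure is in the protocol article under Inclusion and randomisation.

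- Randomisation comes before invitation. Survey respondents "who meet the inclusion criteria will be randomised into invitation lists for intervention group or wait-list control group".
- The lists are ordered at random: "The allocation ratio will be 1:1, and allocated individuals will be placed in random order on the numbered invitation list".
- Invitation follows list order: "The first 40 individuals on each invitation list will receive further information about the trial and be invited to participate". Refusals are handled the same way: "If the invitation is declined, the next person on the given invitation list will be invited".
- Capacity is limited: "a maximum of 40 participants in each group can be included". The Sample size section plans 36 per group.
- The stratification factor is the REHPA score from the survey, and its stated aim is that "randomisation will be stratified to ensure similar proportions of individuals with a score of ≥3 across the invitation lists".

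The text describes no ordering of the lists by stratum and no replacement within stratum. It gives neither the expected list length nor the share scoring ≥3. The only bound on the pool is in the Participants section: "the nationwide survey was distributed to almost 2000 individuals".

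**The concern.** Need for rehabilitation, measured by the REHPA scale, is the only factor the sponsor chose to stratify on. Stratification protects a comparison when it acts on the people compared. Here it acts on two lists that may be much longer than the groups drawn from them. Taking the first acceptors from a randomly ordered list is a random draw, so the share scoring ≥3 can differ between arms by chance even when the two lists match exactly. The longer the lists, the closer this comes to no stratification.

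There is a second route. People are allocated before they are invited, and the two offers differ: the programme now, or standard care for three months first. If willingness to accept depends on rehabilitation need in one arm more than in the other, the gap is systematic, and replacement by the next person on the list does not correct it.

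**Working it through.** **Group size.** The plan gives no figure for balance, so there is none to reproduce. Its group size does reproduce. With an effect of 1.74 and SD of 2.37 (Sample size section), n = 2 × (1.96 + 0.84)² × (2.37/1.74)² ≈ 29.1, rounded up to 30. Then 30/0.85 = 35.3, rounded up to 36 per group.

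**Inputs.** From the article: m = 36 enrolled per arm. Assumed, because not given: share scoring ≥3, p = 0.5 (the value with the largest variance), and list length L from 40 to 200.

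**Formula.** Take two lists of length L with identical counts scoring ≥3, each in random order. The first m people are then a draw without replacement, so

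SD(difference) = √[ 2p(1−p)/m × (L−m)/(L−1) ].

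With no stratification the last factor drops out: √(2 × 0.25/36) = 0.118. The variance removed by list-level stratification is 1 − (L−m)/(L−1).

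| List length L | (L−36)/(L−1) | SD of difference | Variance removed | P(gap ≥15 points), normal approximation |
|---|---|---|---|---|
| 40 | 4/39 = 0.103 | 0.038 | 90% | under 0.1% |
| 60 | 24/59 = 0.407 | 0.075 | 59% | 5% |
| 100 | 64/99 = 0.646 | 0.095 | 35% | 11% |
| 200 | 164/199 = 0.824 | 0.107 | 18% | 16% |
| no stratification | 1 | 0.118 | 0% | 20% |

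With 40 enrolled per arm the SDs are slightly smaller: 0.065, 0.087 and 0.100 for L = 60, 100 and 200, against √(2 × 0.25/40) = 0.112 unstratified.

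**Simulation check** (3000 runs per setting, 36 enrolled per arm). At p = 0.5 the simulated SDs were 0.038, 0.076, 0.089, 0.097 and 0.108 for L = 40, 60, 80, 120 and 200. The mean difference was zero to within simulation error in every setting with equal acceptance. A gap of 10 points or more occurred in 1%, 20%, 27%, 31% and 37% of runs, against 40–41% without stratification. Prevalence of 30% or 70% gave slightly smaller figures (0% at L = 40, 33% at L = 200). Acceptance of 50%, equal in both arms, changed little (27% at L = 80, 36% at L = 200). List length drives the loss, not the refusal rate.

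**Differential acceptance.** Suppose that in one arm 60% of high scorers and 40% of low scorers accept, and in the other arm 50% of each. At p = 0.5 the expected shares scoring ≥3 are 0.30/(0.30 + 0.20) = 60% and 50%, a gap of 10 points. The simulation gave 0.100 at L = 120 and 0.102 at L = 200. If the 60%/40% pattern held in both arms, both shares would be 60% and the expected gap zero. These rates are illustrative.

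**The case against.** The article promises similar proportions across the lists and delivers that; it never claims balance among enrolled participants. Random order is all it states, and an article may leave details of sequence generation to the full protocol. The flow chart is not visible here. All of this is fair, so the point is about a design that could do more, not about a contradiction. A reader might go further and infer that the strata are unbalanced among participants. The documents do not support that: with acceptance alike in both arms, the expected difference is zero, and even the long-list case is no worse than simple randomisation.

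Eligible respondents have already confirmed interest in the programme on specific dates, which should limit refusals and keep the lists shorter. Fewer refusals narrow the room for differential acceptance. They do not remove the chance component, which is present even if everyone invited accepts. Only lists close to 40 would do that.

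Nor does the article show that REHPA ≥3 predicts percentage weight change. As an illustration, if the strata differed by 1 percentage point, a 15-point imbalance would move the treatment contrast by 0.15 × 1 = 0.15, against the 1.74 used in the sample size calculation. A reader might also infer that the analysis ignores REHPA. That cannot be said: Data analysis plans regression on potential confounders with an open list of examples, and refers to a statistical analysis plan that is not shown.

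**Conclusion.** The point holds in a limited form. Balance on REHPA ≥3 is secured for the lists and holds only in expectation for the participants. At p = 0.5 and 36 per arm, the SD of the between-arm difference runs from about 0.04 (lists of 40) to 0.107 (lists of 200), against 0.118 unstratified. List-level stratification thus keeps most of its value if the lists are barely longer than the groups, and loses most of it if they are several times longer. The documents do not settle which applies.

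A systematic gap needs acceptance that depends on REHPA differently by arm. Allocation before invitation makes that possible, but nothing in the article shows that it will happen. It would also be wrong to conclude that the primary test is invalid, because chance imbalance in a baseline factor does not invalidate a randomised comparison. This is a cheap improvement to the design, not a threat to the trial.

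**What to change.** Keep the two invitation lists. Order each in blocks with the same fixed mix of REHPA <3 and ≥3, and replace each decliner with the next person of the same stratum on that list. The difference in share among those enrolled is then limited to what an incomplete last block or an exhausted stratum leaves, and a gap on REHPA from differential acceptance is prevented too. Differential acceptance on other characteristics is not addressed.

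The survey score is already known for everyone randomised, so the cost is a small change to the ordering step and slightly more complex invitation handling: staff need the stratum marked on the list and a rule for when one stratum runs out.

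If the lists are already drawn, include REHPA ≥3 as a covariate in the primary between-group comparison, unless the analysis plan already does so, and report its share by arm among participants.

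Randomising consenters within stratum would also secure the balance, but it would replace the recruitment design and is not needed for this point.

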### Outcome measures and data collection

Outcome measures will be collected at entry, at three, and at six months (Fig. 1). Baseline measurements of the wait-list control group and 6-month follow-up measurements of the intervention group will be performed in one of three regional outpatient clinics depending on the participant’s place of residence. All other measurements will be performed at the rehabilitation centre. Data collected at different time points are shown in Table 2.

**Table 2 Tab2:** Data collection at the different time points in the NUTRI-HAB trial

	TIMEPOINT		
	Baseline	3-month follow-up	6-month follow-up
**DEMOGRAPHIC DATA**			
**Register-based information**			
- Age	X		
- Gender	X		
- Cancer diagnosis	X		
- Time interval since treatment	X		
**Self-reported information**			
- Civil status	X		
- Educational level	X		
- Occupational status	X		
- Current cancer status	(X)	(X)	(X)
- Participation in other rehabilitation services	(X)	(X)	(X)
**NUTRITIONAL RISK AND PRESENCE OF NUTRITION IMPACT SYMPTOMS**			
- NRS 2002	X	(X)	(X)
- PG-SGA SF	X	(X)	(X)
- MDADI	X	(X)	(X)
**REHABILITATION NEEDS MEASURED BY THE REHPA SCALE**			
	(X)	(X)	(X)
**PRIMARY OUTCOME**			
- Body weight	X	X	(X)
**SECONDARY OUTCOMES**			
**Patient-reported outcome measures**			
*Quality of life*			
- EQ-5D-5 L	X	X	(X)
- EORTC QLQ-C30	X	X	(X)
- EORTC QLQ-H&N35	X	X	(X)
*Symptoms of anxiety and depression*			
- HADS	X	X	(X)
**Physical measurements and tests**^**a**^			
- Body mass index	X	X	(X)
- Maximal mouth opening	X	X	(X)
- Hand grip strength	X	X	(X)
- 30-second chair stand test	X	X	(X)
- 6-minute walk test	X	X	(X)

X: Data will be collected for primary analyses, (X): Data will be collected for exploratory analyses

^a^The physical performance tests will be made in a standardised order as follows: 30-second chair stand test, hand grip strength, and 6-minute walk test

EORTC: European Organization for Research and Treatment of Cancer, HADS: Hospital Anxiety and Depression Scale, NRS 2002: Nutritional Risk Screening 2002, PG-SGA SF: The Scored Patient Generated Subjective Global Assessment Short Form, MDADI: M. D. Anderson Dysphagia Inventory

Trained health professionals will perform all physical measurements and tests following strict protocols. Patient reported outcome measures and other patient reported data will be collected through electronic questionnaires distributed through Research Electronic Data Capture (REDCap) [73] to participants’ e-Boks one week before the scheduled physical measurements. Participants without e-Boks will be asked to fill out the questionnaire on a computer on the location of the measurement. Participants who are not confident in filling out the questionnaires electronically will fill out a paper-based questionnaire.

Data from paper-based questionnaires and results from physical measurements and tests will be entered in REDCap by one researcher, and the entered data will be double-checked by a second researcher.

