### Data analysis

The statistical analysis plan for the trial is shown in Additional file 5. Data will be analysed in SAS® Enterprise Guide® 7.1 by both per protocol and intention-to-treat principle [85]. Data analyses will not be commenced until all data collection is completed. A blinded researcher ([name]) will analyse the data, and the project group will interpret results before unblinding. Development in outcome scores from baseline to 3-month follow-up will be calculated for each participant, and differences between intervention group and wait-list control group will be tested using a two-sample two-sided t-test for normally distributed data and Mann-Whitney U test for non-normally distributed data. A significance level of 5% will be applied. Effect size will be estimated with Cohens d [86]. Multiple linear regression will be used to assess the influence of potential confounding variables (e.g. time interval from completion of treatment) on intervention effect. Mean baseline values for outcome scores in both groups will be presented in result tables. Simple linear regression will be used to test correlations between developments in outcome scores and baseline scores in NRS 2002, MDADI or PG-SGA SF. Sensitivity, specificity and predictive values of different cut-offs in NRS 2002, MDADI or PG-SGA SF at baseline in relation to a clinically relevant improvement in outcome scores during participation in the programme will be assessed. To avoid missing data, participants who drop out of the trial will be encouraged to participate in follow-up measurements. The percentage and patterns of missing values in outcome variables will be examined. If data are missing at random and the percentage of missing data is not substantial [87], multiple imputation techniques will be used in the intention-to-treat analyses.

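### Patient-reported baselines are collected after allocation, so the planned change score passes any allocation-related shift into the secondary effects; for the QLQ-C30 a pre-randomisation survey score could serve as a safeguard

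*Protocol article*

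**What the plan says.** **Order of events.** Under Inclusion and randomisation, eligible survey respondents "will be randomised into invitation lists for intervention group or wait-list control group". Information and invitation follow: "The first 40 individuals on each invitation list will receive further information about the trial and be invited to participate".

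**Timing of questionnaires.** Under Outcome measures and data collection (text after Table 2), patient-reported measures are sent to participants' "e-Boks one week before the scheduled physical measurements". For people without the digital mailbox: "Participants without e-Boks will be asked to fill out the questionnaire on a computer on the location of the measurement". Either way, the baseline answers come after allocation.

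**Site of the baseline visit.** The same section states: "Baseline measurements of the wait-list control group and 6-month follow-up measurements of the intervention group will be performed in one of three regional outpatient clinics". It continues: "All other measurements will be performed at the rehabilitation centre". The intervention arm's baseline is therefore at the place where its residential stay is held.

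**Analysis.** Under Data analysis: "Development in outcome scores from baseline to 3-month follow-up will be calculated for each participant". The arms are then compared on this change by t-test or Mann-Whitney test.

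**Survey data.** The self-reliance criterion under Participants uses the self-care item of the QLQ-C30 as answered in the nationwide survey, which covered late effects and health-related quality of life. On the stratification factor, Inclusion and randomisation says: "The REHPA Scale was included in the nationwide survey". The article uses survey data for eligibility, stratification, cancer status and earlier rehabilitation at baseline, and for describing selection. It states no use of survey scores as an outcome baseline or covariate.

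**The concern.** A change score is protected by randomisation only if the arms' baselines can differ by chance alone. Here the baseline answers come from people who have already been invited to one arm. Blinding is described for the researcher who randomises, for the analyst and for the interpretation of results, but not for participants.

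The article itself offers a route by which allocation could affect the answers. Under Intervention, individual counselling is scheduled by needs read from the baseline questionnaires. In the intervention arm, reporting more problems can bring services within days; in the wait-list arm the same answers precede three months of standard care. Disappointment in the wait-list arm could act the other way.

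At stake are the between-arm effects on quality of life and on anxiety and depression, which belong to the first trial objective. If intervention participants answer worse at baseline because of their allocation, the programme looks better than it is. If wait-list participants do, it looks worse.

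**Working it through.** **1. Are the baselines post-allocation?** The sequence in the article is: survey; randomisation to arm-specific lists; invitation; questionnaire about a week before (or at) an arm-specific baseline visit; visit. So the baselines are post-randomisation. That participants know their arm is an inference, though a strong one: someone about to start a five-day residential stay knows it.

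**2. How does a shift pass through?** Let *s* be an allocation-related difference between arms in the baseline answers, in SD units, with no true effect and no difference at month 3.
- Change score: expected difference = 0 − (−*s*) = *s*. All of it is bias.
- Month-3 score adjusted for the visit baseline: bias = *r·s*, with *r* the baseline to month-3 correlation.
- Month-3 score adjusted for a pre-randomisation survey score: bias from *s* = 0.

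**3. Sample size.** The article gives no figure on this point, so only its *n* is used. That *n* reproduces: 2 × [(1.96 + 0.842) × 2.37/1.74]² = 29.1, rounded up to 30 per arm; 30/0.85 = 35.3, rounded up to 36.

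**4. Illustration.** The inputs *s* and *r* are assumptions; the documents give neither. Per arm *n* = 30, so √(2/30) = 0.258.
- SE of the change-score difference = √(2(1 − *r*)) × 0.258, which is 0.258 at *r* = 0.5 and 0.200 at *r* = 0.7.
- SE adjusted for visit baseline = √(1 − *r*²) × 0.258, which is 0.224 at *r* = 0.5 and 0.184 at *r* = 0.7.
- Rejection rate = Φ(b/SE − 1.96) + Φ(−b/SE − 1.96), with b the bias.

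| *s* (SD) | *r* | Change score | Adjusted for visit baseline |
|---|---|---|---|
| 0.1 | 0.5 | 6.7% | 5.6% |
| 0.1 | 0.7 | 7.9% | 6.7% |
| 0.2 | 0.5 | 12.1% | 7.3% |
| 0.2 | 0.7 | 17.0% | 11.8% |
| 0.3 | 0.5 | 21.3% | 10.3% |
| 0.3 | 0.7 | 32.3% | 20.7% |

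With 36 per arm and *s* = 0.2 the change score gives 13.6% (*r* = 0.5) or 19.5% (*r* = 0.7). The rates are the same for a shift in either direction; only the sign of the false finding changes.

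**5. Simulation check.** 20,000 trials per shift, 30 per arm, assumed correlations of 0.7 (survey with visit baseline), 0.6 (survey with month 3) and 0.7 (visit baseline with month 3). Rejection rates for change score, visit-baseline adjustment and survey adjustment were 16.8%, 11.5% and 5.0% at *s* = 0.2, and 31.6%, 19.5% and 5.1% at *s* = 0.3.

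**6. What does survey adjustment cost?** SE = √(1 − *q*²) × 0.258, with *q* the survey to month-3 correlation: 0.207 at *q* = 0.6 and 0.237 at *q* = 0.4. Against the planned change score at *r* = 0.7 (0.200), the variance is 0.64/0.60 = 1.07 or 0.84/0.60 = 1.40 times as large. Against visit-baseline adjustment (0.184) it is 0.64/0.51 = 1.25 or 0.84/0.51 = 1.65 times as large.

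**7. How sharp is an arm-wise check?** Comparing survey-to-baseline change between arms, with a survey to visit-baseline correlation of 0.7, has SE √0.6 × 0.258 = 0.200. A 0.2 SD shift would be significant in only about 17% of trials. The check should therefore be read through its confidence interval, and a non-significant result is not clearance.

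**The case against.** **No shift is shown.** The size, the direction and the correlations are all assumed, and at 0.1 SD with *r* = 0.5 the error rate is 6.7%, close to nominal. This stands: the finding is an unprotected baseline, not a demonstrated bias. A reader might infer that the design favours the programme; the documents do not support a direction.

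**The survey may not hold the needed scores.** A reader might infer that pre-randomisation values exist for every patient-reported outcome and lie unused. The article does not support that. Among the outcome instruments it places only the QLQ-C30 in the survey, strictly through one item; a full QLQ-C30 is a reasonable inference from a survey on health-related quality of life. Nothing places EQ-5D-5L, QLQ-H&N35 or HADS there. The REHPA scale was there but is not an outcome. Survey data also have several stated uses.

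**The analysis plan may already deal with it.** Additional file 5 is not shown and could name such a covariate, and the article foresees multiple regression for confounders. That is possible, but the point does not rest on an omission: the article itself fixes change from the visit baseline as the comparison.

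**Survey adjustment is not a full cure.** A reader might infer that it removes all bias from unblinded reporting. It removes only the part that enters through the baseline. Month-3 answers are also given with the arm known, and wait-list participants give theirs shortly before their own offered stay. The authors acknowledge that wait-list designs may overestimate effects.

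**Baseline means will be tabulated.** This helps little, since a difference in means could also reflect chance or who accepted each invitation. Within-person change since the survey is more specific.

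**Conclusion.** The point holds for the secondary patient-reported outcomes. Their baselines are collected after randomisation and very probably with the arm known, and the planned change score transfers any allocation-related shift one for one. Adjusting for the same visit baseline reduces the transfer to *r·s* without removing it.

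Under assumed shifts of 0.1 to 0.3 SD and correlations of 0.5 to 0.7, with 30 per arm and no true effect, the nominal 5% test rejects in about 7% to 32% of trials. Those figures show sensitivity and do not predict what will happen. Measured body weight is outside the point.

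A survey-adjusted QLQ-C30 analysis is a cheap safeguard, because allocation cannot have affected the survey answers. Whether it should replace the visit-baseline analysis as the main one is debatable, because the survey values are older.

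**What to change.** - For the QLQ-C30 scales, and any other outcome instrument confirmed to be in the survey, pre-specify a linear regression of the month-3 score on arm, the survey score of the same scale and the REHPA stratum. Present it at least as a sensitivity analysis beside the visit-baseline analysis.
- Report survey-to-baseline change by arm, with a confidence interval, as a check for an allocation-related shift.
- For instruments without a survey value, state that the change scores rest on a baseline taken after allocation, and interpret them accordingly.
- State in the report whether participants knew their arm when they answered the baseline questionnaires.

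**Cost.** Analysis-plan wording and one merge with survey data already used for eligibility and stratification. There is some loss of precision: the survey went out in March 2019 with responses accepted for nine weeks, and the trial runs from May 2019, so survey scores are weeks to months older than the visit baseline. Bias in unblinded month-3 answers remains and should be acknowledged.
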